## Abstract

**Background:**

Whether disclosure of a genetic risk score (GRS) for a common disease influences relevant clinical outcomes is unknown. We describe design of the Myocardial Infarction Genes (MI-GENES) Study, a randomized clinical trial to assess whether disclosing a GRS for coronary heart disease (CHD) leads to lowering of low-density lipoprotein cholesterol (LDL-C) levels.

**Methods and design:**

We performed an initial screening genotyping of 28 CHD susceptibility single-nucleotide polymorphisms (SNPs) that are not associated with blood pressure or lipid levels, in 1000 individuals from Olmsted County, Minnesota who were participants in the Mayo Clinic BioBank and met eligibility criteria. We calculated GRS based on 28 SNPs and will enroll 110 patients each in two CHD genomic risk categories: high (GRS ≥1.1), and average/low (GRS <1.1). The study coordinator will obtain informed consent for the study that includes placing genetic testing results in the electronic health record. Participants will undergo a blood draw and return 6-10 weeks later (Visit 2) once genotyping is completed and a GRS calculated. At this visit, patients will be randomized (1:1) to receive CHD risk estimates from a genetic counselor based on a conventional risk score (CRS) vs. GRS, followed by shared decision making with a physician regarding statin use. Three and six months following the disclosure of CHD risk, participants will return for measurement of fasting lipid levels and assessment of changes in dietary fat intake and physical activity levels. Psychosocial measures will be assessed at baseline and after disclosure of CHD risk.

**Discussion:**

The proposed trial will provide insights into the clinical utility of genetic testing for CHD risk assessment.

**Clinical trial registration:**

ClinicalTrials.gov registration number: NCT01936675.

**Electronic supplementary material:**

The online version of this article (doi:10.1186/s12920-015-0122-0) contains supplementary material, which is available to authorized users.

## Background

The potential use of genetic testing for estimating risk of common diseases is of great scientific and public health interest [1]. In one of the first genome-wide association studies (GWAS) [2], common genetic variants in the 9p21 region were associated with coronary heart disease (CHD) with an odds ratio of 1.22 per risk allele. Subsequent meta-analyses in largely European ancestry populations identified additional loci of modest effect sizes associated with CHD [3,4]. The majority of these loci are associated with CHD independent of conventional risk factors and could potentially improve the accuracy of CHD risk estimates. Indeed several studies have reported that a genetic risk score (GRS) based on multiple CHD susceptibility single-nucleotide polymorphisms (SNPs) provides incremental information for CHD risk estimation [5,6].

**Fig. 1 Fig1:**
[figure not shown]
Flow Diagram of the Proposed Clinical Trial. A flow diagram illustrating the design of the MI-GENES study. A total of 2026 individuals from the Mayo BioBank met the eligibility criteria. Among those 2026, a random sample of 1000 individuals was sent for screening genotyping. A total of 968 individuals had valid screening genotyping results. Recruitment was based on screening genotyping results in order to achieve the targeted enrollment goals of ~110 individuals with high GRS (≥1.1) and ~110 with average/low GRS (<1.1) with the expectation that approximately 10-20 study participants are likely to withdraw from the study or be lost to follow-up

However, whether disclosing results of genetic testing for CHD risk influences relevant clinical outcomes is unknown. We describe the design of a randomized trial to investigate whether disclosing a GRS for CHD, based on genotypes of multiple CHD susceptibility SNPs, leads to lowering of low-density lipoprotein cholesterol (LDL-C) levels. The GRS will be incorporated into the CHD risk estimated based on a conventional risk score (CRS) [7]. We will assess whether disclosure of genetic risk for CHD affects LDL-C levels, initiation of statin therapy, changes in dietary fat intake, physical activity levels and psychosocial measures. We will test the following hypotheses: 1) in patients randomized to receive GRS, LDL-C levels at 6 months will be lower than in participants randomized to receive CRS alone; 2) participants with a ‘high’ GRS will have lower LDL-C levels at 6 months than participants in the average/low GRS category and those randomized to receive CRS alone.

A major challenge to implementing genomic medicine is integration of genomic information into the electronic health record (EHR) [8]. As part of this clinical trial, the genetic testing results will be placed in the EHR. Furthermore, we will disclose CHD risk using a decision aid integrated within the EHR to facilitate shared decision making regarding need for statin therapy [9,10]. This decision aid has been modified to include genetic risk information.

## Methods and design

### Overall study design

To maximize information yield from the study, we performed an initial screening genotyping of 28 CHD susceptibility SNPs that are not associated with blood pressure (BP) or lipid levels, in 1000 individuals from Olmsted County who were participants in the Mayo Clinic BioBank and met the eligibility criteria. We calculated GRS for each individual based on these 28 SNPs and stratified individuals into two CHD genomic risk categories: high (GRS ≥1.1), and average/low (GRS <1.1). We will enroll 110 patients in each of the two categories for the clinical trial (Fig. 1). The study coordinator will invite these patients by phone to participate in the randomized trial. He/she will inform patients about the trial, confirm eligibility, and subsequently obtain written informed consent. Specifically, the study coordinator will describe the limitations of genetic testing, the unclear medical benefit of such testing, the format for disclosure of risk, and that the results will be placed in the EHR.

Individuals who agree to participate will undergo a blood draw for genotyping of the CHD susceptibility SNPs in a Central Laboratory Improvement Amendment (CLIA)-certified laboratory. Participants will return 6-10 weeks later (Visit 2) once genotyping is completed and a GRS calculated (Table 1). At this visit, patients will be allocated (1:1) to receive GRS vs. CRS alone and will undergo a 30-min CHD risk counseling session, followed by a visit with a physician for shared decision making regarding statin use. Three months following the disclosure of CHD risk, participants will return (Visit 3) for measurement of fasting lipid levels and assessment of changes in dietary fat intake and physical activity levels. The final study visit (Visit 4) will occur three months after Visit 3. Apart from incorporating the GRS into the CRS in one arm of the study, randomized patients will receive identical exposure to CHD risk education, assessment, and consideration for means of prevention. The study was approved by the Mayo Clinic IRB and is registered at ClinicalTrials.gov (NCT01936675).

**Table 1 Tab1:** Timeline for assessments

Measure	Visit 1	Visit 2	Visit 3	Visit 4
Body mass index				
Waist circumference				
Blood pressure				
Fasting lipid profile				
Fasting blood sugar				
Dietary fat intake				
Physical activity level				
Smoking status				

Visits 2, 3 and 4 occur approximately 2, 5 and 8 months after Visit 1,respectively

### Participants – eligibility requirements

Using validated electronic phenotyping algorithms, we screened 29,352 Mayo Clinic BioBank participants to identify individuals who met the following eligibility criteria: 1) residents of Olmsted County; 2) intermediate risk for CHD, i.e., a 5 %-20 % probability of adverse CHD events over the next 10 years based on the CRS; [7] 3) age 45-65 years without known CHD or CHD risk equivalent (carotid disease, peripheral arterial disease, or abdominal aortic aneurysm); 4) not on statin therapy; 5) self-identified as white ethnicity (since the GRS was derived from SNPs identified in GWAS of largely European ancestry individuals and may not be accurate for non-white individuals); 6) absence of severe comorbidity; 7) no major learning barriers, such as hearing impairment or dementia that would compromise their ability to give written informed consent.

### Screening genotyping

Of the 46 SNPs associated with CHD in GWAS, 29 are not associated with BP or lipid levels [3]. DNA from eligible Mayo Clinic BioBank participants was genotyped for 28 of the 29 CHD susceptibility SNPs on the Veracode Bead Express (Illumina®, San Diego, CA); one SNP (rs3825807) could not be genotyped for technical reasons. Genotype calls were made with Illumina’s GenomeStudio software (http://www.illumina.com), and samples with >98 % call rates across all SNPs on the array were considered for analysis. Samples with lower call rates were rerun as necessary. A GRS for each individual was calculated as previously described, taking into account the average genetic risk in the population [11]. In brief, we assumed an additive genetic model in which the genotypes are coded ‘0’ for non-risk allele homozygotes, ‘1’ for heterozygotes, and ‘2’ for risk-allele homozygotes. A weighted GRS was calculated by multiplying the logarithm of odds ratio for a particular SNP by 0, 1, or 2 according to the number of risk alleles carried by each person. We used a GRS of ≥1.1, i.e., a 10 % or greater increase in risk for CHD, to classify individuals as having ‘high’ GRS. Those with a GRS of <1.1 were classified as having average/low GRS. The “screening” GRS was performed on a research platform and was used to aid in targeted recruitment. After recruitment, GRS was re-calculated for each enrolled study participant based on repeat genotyping at a CLIA-certified laboratory.

### Recruitment and baseline characteristics

To enroll participants in the clinical trial, we will send invitation letters to a random set of patients in the high and average/low GRS categories with a goal of enrolling approximately 110 participants in each category. Assuming 5 %-10 % loss to follow up during the trial, we anticipate a final sample size of at least 200 for the study. At the initial study visit, eligibility criteria will be confirmed and informed consent obtained. We will collect information about demographic factors, educational attainment, race, marital status, medical history, social history, and family history. Participants will complete baseline surveys that assess dietary fat intake, physical activity, and psychosocial measures (Table 2). Height, weight, BP, heart rate, and waist circumference will be measured, and blood will be drawn in the fasting state to extract DNA and to measure lipids and fasting blood sugar. The 10-year probability of CHD will be assessed and calculated at the first study visit based on Wilson et al. [7].

**Table 2 Tab2:** Proposed psychosocial measures

1. Numeracy and perceived risk
2. Attitude towards genetic testing
3. Genetic knowledge and understanding of genetic risk
4. Reaction to risk results and rating of test results information
5. Genetic counseling satisfaction and perceived personal control
6. Shared decision-making and physician visit satisfaction
7. Intention to change
8. Information sharing
9. Recall and decisional regret
10. Anxiety and impact of events

### CLIA Genotyping and calculation of GRS

Twenty mL of blood will be drawn and sent to a CLIA-certified laboratory and DNA will be extracted using standard procedures. All patients will undergo genotyping of the 28 CHD susceptibility SNPs using the TaqMan® procedure (Roche Molecular Diagnostics, Branchburg, NJ). A list of the 28 susceptibility SNPs and the associated genes, if known, is summarized in Table S1 of the Data Supplement. A GRS will be calculated as described above [11] and the CRS will then be multiplied by the GRS to generate an genotype-informed probability of adverse CHD events over the next 10 years (GRS).

### Outcomes

The primary outcome will be the change in LDL-C levels between visit 1 and visit 4. We will also assess whether changes in the LDL-C levels at three months following disclosure of CHD risk. We chose change in LDL-C as the primary outcome because there is a well-established causal association of LDL-C with CHD, both lifestyle changes and drug therapy can modify LDL-C levels, and reduction of LDL-C is a major therapeutic goal in both primary and secondary prevention of CHD. Behaviors related to cardiovascular health, including dietary fat intake and physical activity levels will be assessed at baseline and subsequent study visits to examine any changes over time as a result of receipt of CHD risk information. We will assess several psychosocial measures listed in Table 2. The use of validated measures and selection of instruments previously reported in the genetic literature will enable comparison of the current findings with existing literature [12].

### Sample size and power

In general, studies have confirmed a 5 to 15 % decrease in LDL-C with diet and lifestyle changes and a 30 to 40 % decrease in LDL-C with statin therapy [13,14]. We aimed to detect an LDL-C change of 10 mg/dL to test the first hypothesis that patients randomized to receive GRS would have lower LDL-C levels than patients randomized to CRS alone. For the second hypothesis which will test whether high GRS participants would have lower LDL-C levels that those with low/average GRS and those randomized to receive CRS alone, we aimed to detect an LDL-C change of 15 mg/dL. We assumed the standard deviation of LDL-C change in the entire group to be 25 mg/dL. Under this assumption, the detectable 2-group difference for this change (with 80 % power and 5 % Type I error rate) [hypothesis 1] is 25*sqrt(2/100)*2.8 = 9.9 mg/dL. For hypothesis 2, the detectable decreases in high GRS versus average/low GRS and high GRS versus CRS (with 80 % power and 5 % Type I error rate) are 25*sqrt(2/50)*2.8 = 14 mg/dL and 25*sqrt(1/50 + 1/100)*2.8 = 12.1 mg/dL. Thus, the trial is well-powered to identify an effect of genetic testing that is in the same range as that of diet and exercise.

### Randomization

The second study visit will be scheduled 6-10 weeks after the initial visit to allow for completion of genotyping and calculation of GRS. One of the study staff will allocate patients (1:1) to the two arms, one group receiving genetically informed 10-year CHD risk (GRS) and the other conventional risk factor information alone (CRS). Randomization will be performed by means of a computer-generated random sequence with stratification for age, gender, and positive family history for CHD using the method previously described by Pocock and Simon [15].

### Disclosure of CHD risk

The CHD risk estimate will be disclosed by the genetic counselor during a 30-min semi-scripted session. Patients randomized to GRS will be shown a pictograph that incorporates the revised 10-year CHD risk based on the genotypes of the 28 CHD susceptibility SNPs. The control group will be shown a pictograph based on the CRS. The pictograph depicts 100 people “like the participant” and indicates how many in the next 10 years could be expected to experience an adverse CHD event and how many will not. The genetic counselor will help participants interpret and understand their results, highlighting the probabilistic nature of the genetic testing and that lifestyle factors such as diet, exercise, and smoking are major risk factors for developing CHD. The counselor will encourage participants to sign an action plan for behavioral change that includes increased physical activity and reduced dietary fat intake and smoking cessation if the participant is a smoker. Participants will be provided with a *Frequently Asked Questions* sheet that reiterates the key points conveyed by the genetic counselor at the visit.

### Shared decision making regarding need for statin therapy

Following the visit with the genetic counselor, the patients will see a physician in the preventive cardiology clinic. The physicians will receive training in the use of the decision aid that has been modified to incorporate the genotype-informed estimate of CHD risk. A mock session will be conducted to increase familiarity with the tool. During the patient-physician encounter the focus will be on shared decision making regarding the need for statin therapy. Following this visit, patients will be asked to fill in a questionnaire assessing satisfaction with the physician visit and the shared decision-making process. We will videotape all genetic counselor and physician encounters and assess the fidelity of the genetic counselor and physicians to instructions on the use of the statin choice decision aid [16]. We will use the OPTION instrument [17] to quantify the degree to which physicians involved study participants in the decision making process related to statin therapy. We will also perform qualitative analyses of the videotaped encounters to assess how patients react to genomic results.

### Assessment of changes in psychosocial measures

The participants’ comprehension and perception of CHD risk, their response to genetic risk results, and how they share such information will be assessed by specific surveys. We will measure perceived personal control and decisional regret to better understand ways in which disclosure of genetic testing results affects the individual patient. Such measures will provide novel perspectives on the delivery and receipt of information that will be relevant to counseling and informed consent practice.

### Follow-up

Three and six months after disclosure of CHD risk, participants will return to fill out study questionnaires and undergo a blood draw for fasting plasma lipid levels. At the 6-month visit, participants in the CRS arm will also receive their GRS and will be instructed to discuss their results with their primary care providers. We will review the medical records 6 and 12 months after disclosure of GRS to study participants originally assigned to receive CRS only earlier in the study, to assess whether disclosure of a genotype-informed CHD risk leads to initiation of statin therapy or ordering of additional tests.

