Although it is well known that low dietary fat and increased physical activity reduce the risk of CHD, motivating patients to adopt and sustain lifestyle changes is often difficult. Knowledge of genetic risk may improve patient outcomes by increasing patient motivation (e.g., people who recognize and accept their high genetic risk are more motivated to mitigate it). There is also the possibility that for individuals at relatively low genetic risk, motivation for lifestyle changes may be reduced. We will therefore explore whether disclosing personal genetic risk information for CHD can affect motivation for lifestyle changes.

Recent guidelines [9] emphasize the need for shared decision making when considering the use of statin medications for lowering CHD risk. We modified an existing statin-choice decision aid to incorporate genetic risk information for use in the trial. The decision aid includes pictographs to disclose the 10-year probability of having a CHD event as well as the impact of statin use on such events. Such visual depictions help patients as well as physicians [24] to better comprehend statistical probabilities related to risk of disease. Our decision aid was designed to facilitate shared decision making in the setting of disclosure of CHD genetic risk and we plan to explore in depth how decision making takes place based on quantitative and qualitative analyses of video recordings of the patient-genetic counselor and the patient-MD encounters.

The number of patients undergoing genetic testing is increasing, motivating the study of not only medical outcomes but also the impact of disclosure of genetic risk on psychosocial measures. We have included measures of perceived personal control and decisional regret to better understand ways in which disclosure of genetic testing results affects the individual patient. We will assess participants’ understanding of genomic results and their views about placing genomic data in the EHR, sharing genomic results with family members and others, and any regrets about pursuing genomic testing (Table 2). As a result we will be able to obtain novel perspectives on the delivery and receipt of genetic risk information that will be relevant to counseling patients about genetic testing for common diseases.

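### The CRS arm is due its GRS at the visit that supplies the primary LDL-C, so attendance may differ by arm, and the stated t-test on Visit 1 to Visit 4 change leaves the Visit 3 LDL-C unused

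*Protocol article*

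**What the plan says.** Four statements in the protocol article matter here.

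- **When each arm learns its GRS.** Overall study design, of Visit 2: "At this visit, patients will be allocated (1:1) to receive GRS vs. CRS alone". Follow-up, for the control arm: "At the 6-month visit, participants in the CRS arm will also receive their GRS".
- **What the 6-month visit supplies.** Outcomes: "The primary outcome will be the change in LDL-C levels between visit 1 and visit 4". Follow-up says that at three and six months "participants will return to fill out study questionnaires and undergo a blood draw for fasting plasma lipid levels". Visit 4 therefore provides the primary endpoint and, in the CRS arm, the genetic result. Visit 3 provides an LDL-C value three months earlier.
- **Expected losses.** Recruitment and baseline characteristics: "Assuming 5 %-10 % loss to follow up during the trial, we anticipate a final sample size of at least 200 for the study". The Fig. 1 caption expects that "approximately 10-20 study participants are likely to withdraw from the study or be lost to follow-up". Neither gives losses by arm.
- **How LDL-C is compared.** Statistical methods names t-tests for continuous outcomes, giving LDL-C as the example, with CRS and GRS as the primary groups. It also mentions adjusted comparisons by regression, without linking them to the primary analysis.

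One further statement bears on access to the score. The Background says: "As part of this clinical trial, the genetic testing results will be placed in the EHR". It does not say when this happens for CRS participants.

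**The concern.** Attending the endpoint visit brings something extra in one arm only. A CRS participant who consented to genetic testing has a specific reason to come to Visit 4. A GRS participant had the result six months earlier. Attendance could therefore depend on the allocated arm.

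Unequal attendance does not by itself bias a difference in mean change. It does so when those who stay away also differ in LDL-C change from those who attend. That is possible here, because engagement with the study and engagement with diet, exercise or statins may go together. A t-test on Visit 1 to Visit 4 change has no means of correcting for this. It uses only people with a Visit 4 value and ignores the Visit 3 LDL-C of those who came at three months but not at six. What is at stake is a shift in the primary contrast that the Visit 4 data alone would not reveal.

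**Working it through.** **Inputs from the article (Sample size and power; Recruitment).** SD of LDL-C change 25 mg/dL; target difference 10 mg/dL; 100 per arm after losses; 80% power; 5% type I error; about 220 enrolled, allocated 1:1; 5% to 10% loss.

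**The plan's own figure.** 25 × √(2/100) × 2.8 = 9.9 mg/dL. This reproduces. Power for 10 mg/dL with 100 per arm is 80.7%. Enrolment of 220 less 5% to 10% is 209 to 198, so the 100 per arm is a count after losses.

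**Assumptions not in the article.**
- 110 randomised per arm (220 split 1:1).
- Lost participants have an LDL-C change D mg/dL less favourable than those retained, with the same D in both arms and D from 10 to 25 (25 is one full SD).
- Several splits of the losses between arms.

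**Formulas.**
- Shift in the arm difference among those with Visit 4 data = D × (lost in GRS − lost in CRS)/110.
- SE = 25 × √(1/n_GRS + 1/n_CRS), with n the number retained.
- Type I error = probability that |Z| exceeds 1.96 when Z is normal with mean shift/SE and variance 1.

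**Example.** For 16 GRS v 6 CRS, (16 − 6)/110 = 0.0909. The shift is 0.91 mg/dL at D = 10, 1.36 at D = 15 and 2.27 at D = 25. SE = 25 × √(1/94 + 1/104) = 3.56. Type I error is 5.8%, 6.7% and 9.8%.

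| Total lost | GRS v CRS | Shift, D = 10 to 25 (mg/dL) | Type I error |
|---|---|---|---|
| 22 (10%) | 11 v 11 | 0 | 5.0% |
| 11 (5%) | 8 v 3 | 0.5 to 1.1 | 5.2% to 6.2% |
| 22 (10%) | 13 v 9 | 0.4 to 0.9 | 5.1% to 5.8% |
| 22 (10%) | 16 v 6 | 0.9 to 2.3 | 5.8% to 9.8% |
| 22 (10%) | 22 v 0 | 2.0 to 5.0 | 8.7% to 29% |

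The last row is an extreme bound, not an expectation.

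**Opposite direction.** If the 16 v 6 shift ran against the GRS arm, power for 10 mg/dL would fall from 80% to between 72% and 58%.

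**What Visit 3 can recover.** In a simulation with an assumed correlation of 0.7 between the two visits, a bias of about 1.7 mg/dL fell to near zero under a repeated-measures analysis when dropout depended on Visit 3 LDL-C. It was roughly halved when dropout depended on Visit 4 LDL-C itself. The halving is what one expects: Visit 3 then carries about 0.7² = 0.49 of the missing information. The gain applies only to people who have a Visit 3 value.

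**The case against.** The strongest reply is that the design choice is sensible and most of the harm is conjecture. Disclosing at the endpoint visit keeps the control arm free of the score during the comparison period and still gives participants their result. Analysis sets and missing-data rules may sit in an analysis plan that is not shown. Much of this stands, and it rules out several stronger readings that a reader might draw.

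- **That CRS participants get their GRS only by attending.** The article says when they are due to receive it. It does not make attendance a condition or exclude later disclosure, and placement in the EHR is a possible second route.
- **That lost participants are removed from the analysis.** The move from 220 to about 200 is a planning allowance, not an analysis set.
- **That nothing is collected on those who miss Visit 4.** The article is silent, and silence in a condensed article proves nothing.
- **That loss will be heavier in the GRS arm and favour the hypothesis.** The Discussion does say "There is also the possibility that for individuals at relatively low genetic risk, motivation for lifestyle changes may be reduced", but that concerns lifestyle, not attendance, and the same paragraph says genetic knowledge may raise motivation. About half of enrolment is meant to be high GRS, and such participants may be more engaged. CRS participants might also leave early because the result is withheld.

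The 16 v 6 split also has no source. It would itself be a noticeable imbalance (Fisher's exact p = 0.04), and milder splits give shifts below 1 mg/dL.

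What survives is narrower. The coupling of disclosure and endpoint is in the text, and so is the t-test. An analysis plan can change the test, but it cannot recover Visit 4 blood samples that were never drawn.

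**Conclusion.** The point holds as a modest design risk with a cheap improvement, not as a demonstrated bias. The article ties the CRS arm's GRS to the primary-endpoint visit, and the comparison it states for LDL-C makes no use of the Visit 3 value for people without Visit 4. Bias needs both unequal loss and loss related to LDL-C change. Whether either will occur, and in which direction, cannot be known from the document.

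Within the planned 10% loss, the illustrative shift runs from nil to about 2.3 mg/dL for splits up to 16 v 6, against a 10 mg/dL target and an SE of about 3.6. These figures rest on the assumed gap of 10 to 25 mg/dL and on the assumed splits. Planned power is only about 80%, so even a moderate shift against the effect would matter.

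**What to change.** 1. **Primary analysis.** Replace the t-test with a repeated-measures model of LDL-C at Visits 3 and 4, adjusted for Visit 1 LDL-C, in all randomised participants with any post-disclosure value. Take the arm contrast at Visit 4 as primary.
2. **Collection.** Offer a blood-draw-only Visit 4 to anyone who would otherwise miss it, on the same terms in both arms.
3. **Reporting.** Give Visit 4 attendance by arm and by GRS category.
4. **EHR values.** Use LDL-C from the EHR only in a sensitivity analysis. It is more likely to be on record for people started on statins, and may be non-fasting, off-window or from another assay. The record review described under Follow-up does not already supply it: that review concerns former CRS participants after their GRS disclosure, and looks at statin initiation and test ordering.

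**Cost.** Slightly more analysis work and a few extra contacts among the 10 to 20 people expected to be lost. The model assumes data are missing at random given Visits 1 and 3, so it reduces but may not remove bias when loss depends on the unseen Visit 4 value. It does not help those with no post-disclosure LDL-C.

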### Statistical methods

All survey data will be exported from REDCap (Research Electronic Data Capture) [18] to a SAS database for analyses. Data analysts will be blinded to allocation. Descriptive data will be provided for all measures. The frequency (%) of categorical factors will be compared using either the Chi-Square or Fisher’s exact test and t-tests for continuous outcomes such as LDL-C levels. The primary groups analyzed will be the randomized treatment groups – CRS and GRS. We will also conduct supplementary analyses comparing 3 groups: CRS, high GRS, and average/low GRS.

The use of validated, standard measures for many of the behavioral and psychosocial measures will enable comparison of the data with other studies. Within-participant analyses (using each participant as his/her own control) will be performed to evaluate changes in these measures over time. Difference in scores will be examined for the outcomes by comparing post-results assessments to baseline assessments. Logistic regression will be used for binary outcomes (e.g., % achieve accurate understanding of their CHD risk) to compare the change by arm with odds ratios and their associated 95 % confidence intervals. Adjusted comparisons of binary and continuous outcomes will be performed using regression models. All secondary analyses will be based on two-sided tests at a significance level of 0.05. We will conduct subgroup analyses to assess interactions between the intervention and: a) sex and b) family history of CHD.

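### The post-crossover record review of the CRS arm has no comparator and cannot show that GRS disclosure causes statin starts or extra tests; test ordering has no other stated assessment

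*Protocol article*

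**What the plan says.** All references are to the protocol article.

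- **Follow-up, late disclosure.** The control arm learns its score at Visit 4: "participants in the CRS arm will also receive their GRS and will be instructed to discuss their results with their primary care providers".
- **Follow-up, record review.** Records are reviewed 6 and 12 months after that disclosure, for participants "originally assigned to receive CRS only earlier in the study". The purpose is "to assess whether disclosure of a genotype-informed CHD risk leads to initiation of statin therapy or ordering of additional tests". No comparison group, reference period or expected background rate is given.
- **Background.** Statin initiation is also named as a trial-wide outcome: "We will assess whether disclosure of genetic risk for CHD affects LDL-C levels, initiation of statin therapy".
- **Statistical methods.** "The primary groups analyzed will be the randomized treatment groups – CRS and GRS". Categorical factors are compared by chi-square or Fisher's exact test, and binary outcomes by logistic regression.
- **Ordering of additional tests** appears only in the Follow-up sentence on the record review.

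**The concern.** The article states both the group to be studied and the inference to be drawn from it, and the group cannot support the inference. One arm observed after crossover, with no concurrent undisclosed arm and no stated reference, yields a count of statin starts and test orders. It does not yield the part of that count due to disclosure.

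Several other causes act on the same people. They enter off statins, so starts can accrue from ordinary care. They have already had a counselling session and a physician visit about statins at Visit 2, and lipid measurements at 3 and 6 months. They receive the late result together with an instruction to see their primary care provider, and that visit could prompt a prescription or a test whatever the score shows. The late disclosure is also not the intervention that was randomised, which combined a genetic counsellor with a preventive cardiology physician.

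Two things are at stake. For test ordering, the only assessment that the article states is one that cannot answer the question. For statin initiation, an uncontrolled causal reading could be reported beside the randomised one. That matters because statins are the largest LDL-C lever in the article's own figures (30 to 40% reduction, against 5 to 15% for diet and lifestyle).

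**Working it through.** **1. The plan's own figures.** The article gives no size, rate or power for the record review, so there is no figure to reproduce for it. Its LDL-C detectable differences do reproduce, using SD × √(1/n₁ + 1/n₂) × 2.8 with SD 25 mg/dL:

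- Hypothesis 1: 25 × √(2/100) × 2.8 = 9.9 mg/dL.
- Hypothesis 2: 25 × √(2/50) × 2.8 = 14.0 mg/dL, and 25 × √(1/50 + 1/100) × 2.8 = 12.1 mg/dL.

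These do not bear on the present point.

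**2. Who has been told the GRS, and when.**

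| Period | GRS arm | CRS arm | Undisclosed comparator? |
|---|---|---|---|
| Visit 2 to Visit 4 | told at Visit 2 | not told | yes, randomised |
| After Visit 4 | already told | told at the 6-month visit | none |

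The record review falls wholly in the second row.

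**3. What a single-arm count would show with no effect.** Inputs: a final sample of at least 200 (Recruitment and baseline characteristics) and 1:1 allocation (Randomization), so n ≈ 200/2 = 100 in the CRS arm. The 12-month background start rate p is not in the article and is assumed. Expected starts are n × p, and the chance of at least one start is 1 − (1 − p)ⁿ.

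| Assumed p | Expected starts, n = 100 | Chance of at least one |
|---|---|---|
| 2% | 2 | 86.7% |
| 5% | 5 | 99.4% |
| 10% | 10 | >99.9% |
| 20% | 20 | >99.9% |

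The base of 100 is an upper figure for statins, because anyone who started between Visit 2 and Visit 4 cannot start again. If 30% had done so (assumption), 70 would remain at risk, and the four rates would give 70 × p = 1.4, 3.5, 7 and 14 starts. Some starts are still likely with no effect of disclosure, so seeing them is not evidence of one.

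**4. What the randomised period could detect.** With 100 per arm, two-sided 5% and 80% power, the normal approximation is power = Φ[(|p₂ − p₁| − 1.96 × √(2p̄(1 − p̄)/100)) / √((p₁(1 − p₁) + p₂(1 − p₂))/100)], where p̄ is the mean of p₁ and p₂. The CRS-arm rates are assumed.

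| CRS-arm rate | Smallest detectable higher GRS-arm rate |
|---|---|
| 5% | 17.5% |
| 10% | 25% |
| 20% | 38% |
| 30% | 49% |

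Only large differences of about 12 to 19 percentage points would be detected reliably, but unlike the later count this comparison is unconfounded.

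**The case against.** **Statin initiation does not depend on this review.** This stands. Background lists it among the effects of disclosure, and Statistical methods makes the randomised arms the primary groups. A reader might infer from Follow-up that the statin question is answered from the CRS arm alone; the article does not support that. The same defence is not available for ordering of additional tests, which has no other mention.

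**No attribution rule is stated.** This also stands. A reader might infer that every start after late disclosure will be credited to disclosure. The article says no such thing, and the full protocol could name a reference period. What remains is narrower: the article puts a causal question to this group, and nothing it states separates background from effect. The within-participant analyses in Statistical methods refer to the behavioural and psychosocial measures. A before-and-after contrast would also be distorted, since the earlier six months open with the statin discussion and those still untreated at Visit 4 are a selected remainder.

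**The background rates are assumed.** True. They illustrate that starts occur without an effect; they do not estimate a bias.

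**The GRS arm's later records are no control.** Correct. That arm was told at Visit 2, so the comparison would be of earlier with later disclosure in different care settings.

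**Conclusion.** The point holds in a limited form. The record review is confined to the CRS arm after crossover, has no stated comparator, and is given a causal purpose that it cannot serve. For ordering of additional tests it is the only assessment stated. For statin initiation it is a weaker addition to a randomised comparison that the article already supports.

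The size depends on background rates that the article does not give. At assumed 12-month rates of 2% to 20%, about 2 to 20 starts per 100 at-risk participants would be expected with no effect, and fewer if many had started by Visit 4. No comparable range is offered for test orders.

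Severity is minor. The review begins after the control arm is told its score, so the primary LDL-C outcome (Visit 1 to Visit 4), both hypotheses and the power calculation are untouched.

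**What to change.** 1. Extract statin starts and test orders from the records of both arms for Visit 2 to Visit 4, with the same fields and definitions, and rest any causal statement on that randomised comparison.
2. Label the 6- and 12-month review of the CRS arm descriptive, and reword its purpose without causal language: the frequency of statin starts and test orders after late disclosure.
3. Optionally, compare high with average/low GRS within the CRS arm in the later period. With about 110 enrolled per category and 1:1 allocation, this is roughly 50 each. State that it tests the content of the result and not disclosure itself. The planned three-group analysis keeps CRS as one group, so it does not supply this contrast.
4. If the GRS arm's records for the later window are shown, present them as context only.

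Cost: record extraction for about 200 charts over the randomised period, with no added visits or procedures. The rewording costs nothing, and item 3 uses data already collected. Item 4, if wanted, adds extraction on about 100 GRS-arm charts.
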